## 5.8 CLCE-24

The Checklist for Cognitive and Emotional Consequences (CLCE-24) is recorded at 90 and 180 days. The CLCE-24 instrument consists of 24 questions with possible responses of 'No', 'Yes, but not severe', 'Yes, severely hindering daily life' and 'I am not sure'. The problems are split into cognitive problems, corresponding to the first 13 questions, and emotional problems, corresponding to the next 9 questions. The final 2 questions solicit information on

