## EVG001SAH Statistical Analysis Plan

other specified problems; these will not be used in the analysis. Data will be analysed separately for emotional and cognitive problems. The number of questions, within each subscale, that has a response of either ‘Yes, severely hindering daily life’ or ‘Yes, but not severe’ will be calculated and this number will be recoded to a CLCE score as described in Table 7. The CLCE-24 score will be subject to statistical analysis.

If a patient dies before a given timepoint they will be assigned a score of 3. If less than 50% of the CLCE-24 questions are completed at a given timepoint the data will not be included in the analysis for that patient at that timepoint. Otherwise, the percentage of responses will be calculated using 24 as the denominator. In determining evaluability, a response of ‘I am not sure’ will be considered a completed response.

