| Triple H Therapy                 | Proportion of patients with hypertensive (Triple H) therapy                                                                                                                                                                                                                                                                                                        |
| SF-36                            | Physical and Mental Health scores at Day 28, 90 and 180.

Sensitivity analysis: 
 
If more than 15% of patients have missing data at Day 180 in either treatment arm, missing data diagnostics performed.
 
                                                                                                     |
| CLCE-24                          | Score based on the percentage of Cognitive and Emotional questions at Day 90 and 180 that indicate problems that severely hinder daily life

Sensitivity analysis: 
 
If more than 15% of patients have missing data at Day 180 in either treatment arm, missing data diagnostics performed.
 
                  |
| BICRO-39                         | Primary: overall BICRO score at Day 90 and 180

Supplementary analyses: 
 
8 subscale scores at Day 90 and 180
 
 Sensitivity analysis: 
 
If more than 15% of patients have missing data at Day 180 in either treatment arm, missing data diagnostics performed.
 
 |
| SAHOT                            | SAHOT category at Day 28, 90 and 180

Sensitivity analysis: 
 
If more than 15% of patients have missing data at Day 180 in either treatment arm, missing data diagnostics performed
 
                                                                                                                          |
| Length of Acute Hospital Stay    | Primary: including patients who die prior to discharge censoring them 1 day longer than the largest observed stay

Sensitivity analysis; 
 
Censoring at the date of death as end of hospital stay for patients who die prior to discharge
 
                                                                    |

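### CLCE-24 subscales of 13 and 9 items are scored over 24, so no living patient can reach the worst emotional category and blank items count as no problem

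*SAP*

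**What the plan says.** Section 5.8 describes a 24-question instrument. It divides the content as follows: "The problems are split into cognitive problems, corresponding to the first 13 questions, and emotional problems, corresponding to the next 9 questions". The last two questions ask about "other specified problems; these will not be used in the analysis". It continues: "Data will be analysed separately for emotional and cognitive problems", and it counts the problems reported within each subscale, whether or not they are severe. Table 7 converts the percentage to a score: 0% gives 0, above 0% and below 25% gives 1, 25% to below 50% gives 2, and 50% or more gives 3.

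Three further rules in Section 5.8 matter here:

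- **Death:** "If a patient dies before a given timepoint they will be assigned a score of 3".
- **Evaluability:** a patient's data are dropped at a timepoint only if fewer than half of all the CLCE-24 questions are completed. An unsure answer counts as completed.
- **Denominator for evaluable patients:** "Otherwise, the percentage of responses will be calculated using 24 as the denominator".

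Section 6.5 analyses the score by proportional odds regression at each timepoint. In Section 6.2, Table 11 describes the score as based on "questions at Day 90 and 180 that indicate problems that severely hinder daily life", with no mention of the milder answer.

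**The concern.** The numerator comes from one subscale and the denominator from the whole instrument, including two questions the plan says it will not use. The percentage then cannot run from 0 to 100, and the Table 7 cut-points no longer mean what they say. If programmed as written, the emotional outcome loses its worst category for living patients, and the ordinal model treats that level as mortality alone.

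A fixed denominator also gives an unanswered item the same value as an answer of no problem. No rule requires any answers within a given subscale, so a patient can be scored on emotional problems without having answered one emotional question. Such a patient has a score, so on a natural reading would not count as missing towards the 15% trigger for missing-data diagnostics in Section 6.7.

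The Table 11 wording adds a second ambiguity: a programmer working from it would count only the severe answers.

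**Working it through.** **Inputs (Section 5.8 and Table 7).** Cognitive items 13; emotional items 9; unused items 2; total 13 + 9 + 2 = 24. Denominator 24. Table 7 cuts at 25% and 50%. Evaluable if at least 12 of 24 questions are completed.

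**Where 24 comes from.** It is the item count of the whole instrument. It is not the size of either subscale, nor the number of items used (13 + 9 = 22).

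**Largest possible percentages over 24.**
- Emotional: 9/24 = 37.5%, below 50%, so score 3 is unreachable.
- Cognitive: 13/24 = 54.2%, so score 3 is only just reachable.

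**Counts needed.** Over 24, the 25% cut falls at 24 × 0.25 = 6 problems and the 50% cut at 24 × 0.50 = 12. Over the subscale's own size, the cuts are:
- emotional: 9 × 0.25 = 2.25, so 3 problems; 9 × 0.50 = 4.5, so 5 problems
- cognitive: 13 × 0.25 = 3.25, so 4 problems; 13 × 0.50 = 6.5, so 7 problems

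Running every possible count through Table 7, with all items answered, gives:

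| Score | Emotional, over 24 | Emotional, over 9 | Cognitive, over 24 | Cognitive, over 13 |
|---|---|---|---|---|
| 0 | 0 | 0 | 0 | 0 |
| 1 | 1–5 | 1–2 | 1–5 | 1–3 |
| 2 | 6–9 | 3–4 | 6–11 | 4–6 |
| 3 | none | 5–9 | 12–13 | 7–13 |

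The score differs for emotional counts 3 to 9 (7 of the 10 possible counts) and cognitive counts 4, 5 and 7 to 11 (7 of 14). In each case the score over 24 is the better one. At an emotional count of 5 it differs by two categories (1 against 3).

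**Blank items.**
- Five emotional items answered, all problems, four blank: 5/24 = 20.8%, score 1. Over answered items, 5/5 = 100%, score 3.
- Eleven cognitive items answered, all problems, two blank: 11/24 = 45.8%, score 2. Over answered items, 11/11 = 100%, score 3.
- All 13 cognitive items answered, no emotional item answered: 13/24 = 54.2% complete, so evaluable. Emotional percentage 0/24 = 0%, score 0, the best category.

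**Alternative readings.**
- *24 applies to the completeness check only.* The sentence is introduced as what happens once that check has been passed, and it refers to the percentage named in the Table 7 heading. The text does not support this reading.
- *24 was meant for one pooled score.* The maximum would be 22/24 = 91.7%, which would make the cut-points reachable, but it contradicts the separate analysis of the two subscales.
- *22 was meant.* 9/22 = 40.9%, so emotional score 3 is still unreachable.

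**The SAP's other questionnaires.** SF-36 (5.7) and BICRO-39 (5.9) average the answered items within a subscale, and SAHOT (5.10) scales up within a subscale. All three exclude the data when a contributing subscale is empty. CLCE-24 has neither safeguard.

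**The case against.** The contradiction itself is hard to dispute. The case on the other side concerns how much it matters.

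- **Importance.** CLCE-24 is neither the primary endpoint nor one of the two key secondaries, which are mRS and GOSE at 90 days (Section 6.3). It is analysed initially in the per-protocol population only. This stands: no primary, key secondary or safety conclusion rests on it.
- **Bias.** The same mapping applies to both arms. Shifted cut-points alone cost resolution and distort labels; they do not by themselves favour one arm. Crediting blanks would bias the comparison only if item non-response differed between arms, and the SAP cannot show that. This stands too. The misclassification is in the absolute scores, and the direction of any effect on the odds ratio is unknown.
- **A death-only worst level.** mRS, GOSE and SAHOT have one by design. True, but those scales define it openly. Table 7 defines score 3 as 50% or more of responses and has no row for death. The fault is that the derivation departs from its own table.
- **The intended denominator.** Table 7 does not say what the percentage is of, and the reference list gives no CLCE source. The subscale denominator is therefore an inference. It is the only reading that fits both the within-subscale count and the separate analyses.
- **Table 11.** It is a summary, and Section 5.8 and the Table 7 heading agree on the numerator. This is fair: the mismatch needs aligning but is the lesser part of the point.

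**Conclusion.** The concern holds. As written, the emotional score cannot reach 3 in a living patient (maximum 37.5%), the cognitive score reaches 3 only at 12 or 13 of 13 items, and an empty emotional subscale can be scored as the best outcome. Taking the subscale's own size as the intended denominator, 7 of 10 emotional counts and 7 of 14 cognitive counts receive too favourable a score, at both Day 90 and Day 180. Table 11 separately contradicts Section 5.8 on which answers count.

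How many patients would be affected depends on the distribution of problem counts and blanks, which the SAP does not give. The effect is confined to two non-key secondary outcomes. The rule should still be corrected before it is used, because choosing a denominator or numerator after unblinding would be open to challenge as data-driven.

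**What to change.** In Section 5.8:

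1. Define the percentage, separately for each subscale, as 100 × (items reporting a problem) / (items completed in that subscale). A fixed 9 or 13 would make score 3 reachable but would still credit blanks as no problem.
2. Judge completeness per subscale: at least 50% completed, which is 7 of 13 cognitive and 5 of 9 emotional items. Excluding only empty subscales, as for SF-36, would match the SAP's other rules more closely. With an answered-item denominator, however, one answered item reporting a problem would give 1/1 = 100% and score 3, so a real minimum is preferable.
3. State how an unsure answer is handled. It now counts as completed but not as a problem, so under item 1 it would stay in the denominator and lower the score. Either keep that deliberately or remove it from the denominator.

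In Table 11, make the description agree with Section 5.8 and Table 7 on whether the milder problem answers count.

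Optionally, give death its own category 4 so that it does not tie with living patients in score 3. This is a design choice and is not needed to cure the defect.

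The cost is a few sentences of SAP text and trivial programming, with no new data. CLCE-24 belongs to the second analysis, but Section 4 has the TCD data analysed after the first data cut-off. The amendment is best dated before that first analysis.

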**Table 7. CLCE-24 Score**

| Percentage of responses recorded as ‘Yes, severely hindering daily life’ or ‘Yes, but not severe’ | Score assigned for analysis |
|---------------------------------------------------------------------------------------------------|-----------------------------|
| 0%                                                                                                | 0                           |
| 0% < to < 25%                                                                                     | 1                           |
| 25% ≤ to < 50%                                                                                    | 2                           |
| ≥50%                                                                                              | 3                           |

## 5.9 BICRO-39

The Brain Injury Community Rehabilitation Outcomes Scale (BICRO-39) is recorded at 90 and 180 days and consists of 39 questions scored from 0= the most favourable response (no help or prompts, once a week or more, most or all days, several hours a day, more than 20 hours a week, never - as appropriate) to 5=the least favourable response (don’t do at all, not applicable or never, almost always – as appropriate). The BICRO-39 is divided into 8 subscales as presented in Table 8. The subscale score is calculated as the mean of the individual scores within that subscale.

An overall score will also be calculated as the mean score across the 34 individual scores that are not included in the contact with partner/children and contact with parents/siblings subscales. These scales are excluded as the desirable direction may vary between patients; some patients may wish to be less reliant on carers if they are relatives and in others alienation from family member maybe a problem^6.

Any patient who has died before the respective timepoint will be assigned a subscale and an overall score of 5 corresponding to the worst outcome. If less than 50% of the 39 questions are completed at a given timepoint, or no questions have been answered in one of the 6 subscales contributing to the overall score, none of the BICRO-39 data will be included in the analysis at that timepoint. Otherwise, if ≥50% but less than 100% of the BICRO-39 questions are completed, the mean of the recorded scores within the respective subscales will be used in the analysis of subscales. However in this case, the overall score will be calculated as a weighted average of the individual subscale scores with weights of 6/34 for all subscales included apart from productive employment which receives a weight of 4/34. This approach ensures that if missing data predominates in one subscale its contribution is not down-weighted in the overall score.

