### 6.2 Analysis Methods

Each endpoint subject to formal statistical analysis is listed in Table 11. To investigate the robustness of the primary analysis of each endpoint additional analyses will be performed. These are described as sensitivity analyses if they assess whether the results are influenced by departures from assumptions made in the primary analysis and are described as supplementary analyses if they assess a closely related measure not considered as important as the one chosen in the primary analysis.

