### **6.3 Multiplicity**

The primary endpoint is the maximum post-dose MCA mean flow velocity.

Whilst no formal multiplicity adjustments will be made amongst the secondary endpoints, the two key secondary endpoints are:

- 1) Modified Rankin Score at 90 days
- 2) GOSE score at 90 days

Individual BICRO subscales will not be considered statistically significant unless the overall BICRO score is also statistically significant at the same timepoint.

The TCD data will be analysed in advance of the other secondary endpoints. However, given that each endpoint will be analysed only once no adjustments will be made to the significance levels for each endpoint.

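### Two BICRO-39 family-contact subscales, left out of the overall score because they have no uniform direction of benefit, are still formally tested with 5 as worst and deaths scored 5

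*SAP*

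**What the plan says.** - **Overall score (SAP Section 5.9).** It is the "mean score across the 34 individual scores that are not included in the contact with partner/children and contact with parents/siblings subscales". The reason given is "These scales are excluded as the desirable direction may vary between patients". The SAP explains that some patients may want to depend less on relatives who act as carers, while for others estrangement from family may be the problem.
- **Item scoring (Section 5.9).** The instrument "consists of 39 questions scored from 0= the most favourable response", and 5 is the least favourable. No exception is made for the contact items.
- **Deaths (Section 5.9).** A patient who has died before the timepoint "will be assigned a subscale and an overall score of 5 corresponding to the worst outcome". Again there is no exception for the contact subscales.
- **What is tested (Section 6.2, Table 11).** "Each endpoint subject to formal statistical analysis is listed in Table 11". The BICRO-39 row gives the overall score as primary and, as supplementary analyses, "8 subscale scores at Day 90 and 180".
- **Method (Section 6.5).** BICRO is analysed with Van Elteren's test, and the effect is given as an unstratified Hodges-Lehmann difference with a 95% confidence interval. No subscale is exempted.
- **Gate (Section 6.3).** "Individual BICRO subscales will not be considered statistically significant unless the overall BICRO score is also statistically significant at the same timepoint".

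**The concern.** The reason for keeping the five contact items out of the overall mean is that a higher or lower score is not better for everyone. That reason applies with more force when those items stand alone as an endpoint. Yet the scoring and the death rule treat 5 as worst on these subscales, and the planned test and estimate treat them like the other six. The SAP never says how a difference on them is to be read.

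Two things follow. First, the Hodges-Lehmann estimate will have a sign, but on the SAP's own reasoning that sign cannot be labelled benefit or harm. Second, the death rule combines an outcome that is clearly worst with a survivor measure that has no agreed direction. A difference could therefore come from mortality, from a change in contact, or from the two pulling against each other. The stake is how a few supplementary results are interpreted, not the trial's main conclusions.

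**Working it through.** **Reproducing the plan's item count.** Table 8 gives 6 + 6 + 6 + 2 + 3 + 6 + 4 + 6 = 39 items in 8 subscales. Removing the contact subscales gives 39 − 2 − 3 = 34, as stated. The weights used when items are missing also check: 5 × 6/34 + 4/34 = 34/34 = 1. So neither contact subscale enters the overall score by any route.

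**Counting the affected tests.** All subscale tests: 8 × 2 timepoints = 16. Contact subscale tests: 2 × 2 = 4. Remaining after the fix: 6 × 2 = 12.

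**Setting the provisions side by side.**
1. Section 5.9, overall score: direction differs between patients, so the items are excluded.
2. Section 5.9, item scoring and death rule: direction is fixed, with 5 as worst.
3. Table 11 and Section 6.5: the subscales are tested and estimated like the others.
4. Section 6.3: a subscale may be called significant only if the overall score is significant at that timepoint. This limits claims of significance. It supplies no direction, and the score that opens the gate holds no information on either contact subscale. Section 7 presents the results of the secondary analyses whether or not the gate opens.

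Provision 1 conflicts with provisions 2 and 3, and provision 4 does not resolve the conflict. By contrast, Section 5.10 does handle a question of this kind in SAHOT: the relationship-quality question is scored 0 when a follow-up question shows that the relationship is better. BICRO-39 has no such rule.

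**Illustration of the mixing, on assumed inputs.** The SAP gives no death rates or contact scores, so these are assumptions: 45 patients per arm (90 evaluable, split equally); survivor scores normal with mean 2.5 and SD 1.3, rounded to half points and clipped to 0–5; deaths scored 5; unstratified Wilcoxon test at two-sided 5%; 2,000 runs; gate ignored. Differences are active minus placebo.

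| Deaths, placebo v active | Shift in survivors' score on active | Rejection rate | Mean Hodges-Lehmann difference |
|---|---|---|---|
| 10% v 10% | 0 | 4.8% | 0.00 |
| 20% v 10% | 0 | 11.5% | −0.23 |
| 20% v 5% | 0 | 21.7% | −0.36 |
| 10% v 10% | +0.8 | 65% | +0.71 |
| 10% v 10% | −0.8 | 61% | −0.73 |
| 20% v 10% | +0.5 | 8.3% | +0.15 |

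Rows 2 and 3 show that mortality alone can move the result when survivors' contact is the same in both arms. Rows 4 and 5 show that a shift in either direction can be detected, yet Section 5.9 gives no ground for calling either one better. In the last row the two components partly cancel. The rates depend on the assumptions and are not forecasts for this trial.

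**The case against.** The case for leaving the plan alone has substance.

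- **The sign is not meaningless.** The test is two-sided against no difference, and the estimate can be read on the 0–5 scale as more or less contact. A reader might infer that the result has no interpretable direction at all. That goes too far: what is missing is a uniform direction of benefit, and among survivors the sign keeps its descriptive meaning.
- **The SAP has already contained most of the problem.** It names the direction issue, keeps the items out of the main BICRO analysis, ranks the subscales as supplementary and gates them. It nowhere says that a contact difference will be reported as benefit or harm. This stands, and it is why the point is minor.
- **Scoring death as worst is this SAP's convention.** It is used for mRS, GOSE, SF-36, CLCE-24, SAHOT and the other BICRO subscales. Sensitivity to mortality is therefore not a fault peculiar to these two scales. What is peculiar to them is that death is joined to a survivor measure whose own direction the SAP disclaims.
- **Not-applicable answers.** A reader might infer that a survivor without a partner or children scores the same as a patient who has died, because the anchors scored 5 include "not applicable or never, almost always". The document does not support that firmly. It lists anchors for several item types together, to be used as appropriate, and does not say which items carry which anchor. Not applicable and never also appear as one anchor, so setting such answers aside could discard genuine absence of contact. The largest shift that one such answer could cause in one patient's subscale mean says nothing about a difference between arms.
- **Summaries in survivors condition on an outcome after randomisation.** True, which is a reason to keep them descriptive.

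**Conclusion.** The inconsistency is real and narrow. Section 5.9 says that the desirable direction of the two contact subscales varies between patients, while its scoring and death rules, Table 11 and Section 6.5 treat them as ordinary endpoints with a worst end. As a result, 4 of 16 supplementary tests have no uniform direction of benefit and mix mortality with survivor contact. The Section 6.3 gate limits claims of significance but does not settle direction.

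This conclusion rests on the text of the SAP alone. It does not depend on the simulated figures, nor on which items carry the not-applicable anchor. The primary endpoint, the key secondary endpoints (mRS and GOSE at 90 days) and the overall BICRO score are unaffected. It is a minor point, worth correcting because the correction is nearly free.

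**What to change.** 1. **Table 11, BICRO-39 row.** Replace the supplementary analysis of all subscales with: *the 6 subscale scores contributing to the overall score, at Day 90 and Day 180*. Section 5.9 already refers to this set of six in its missing-data rule.
2. **Section 5.9.** Add: *The two contact subscales will be summarised descriptively by arm and timepoint, without a formal test. Deaths will be reported separately and will not be scored 5 on these subscales. Differences on them will not be interpreted as benefit or harm.* The death rule should then be limited to the other six subscales and the overall score.
3. **Section 6.5.** State that the BICRO methods apply to the overall score and those six subscales.

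The tables should label the contact summaries as describing survivors, since they are not a comparison of the arms as randomised. The cost is a few lines of text and four supplementary tests (16 down to 12). The 34-item overall score and its analysis stay as they are.

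### One blank contributing BICRO-39 subscale removes all of the patient's other BICRO-39 subscale scores at that visit, although these are analysed separately

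*SAP*

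**What the plan says.** Section 5.9 sets two conditions for using a patient's BICRO-39 form at a visit.

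- The first concerns the whole form: "If less than 50% of the 39 questions are completed at a given timepoint", the form is not used.
- The second works at subscale level: the form is also not used if "no questions have been answered in one of the 6 subscales contributing to the overall score".

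If either condition fails, "none of the BICRO-39 data will be included in the analysis at that timepoint".

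If both are met but the form is incomplete, "the mean of the recorded scores within the respective subscales will be used in the analysis of subscales". The overall score is then a weighted average of six subscale scores, with "weights of 6/34 for all subscales included apart from productive employment which receives a weight of 4/34". The two family-contact subscales are left out of the overall score.

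Table 11 (Section 6.2) names the overall score as the primary BICRO-39 analysis and lists "8 subscale scores at Day 90 and 180" as supplementary analyses. Under Section 6.3 a subscale result counts as significant only if the overall score is significant at the same visit.

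**The concern.** The second condition protects the overall score, which cannot be formed under the stated weights if one of its six parts is absent. Its consequence reaches further than that purpose. It also removes subscale scores that can be calculated in full and that have an analysis of their own.

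At stake is observed data. Each affected survivor drops out of up to seven subscale comparisons because of a gap in an eighth. (Patients who have died are assigned the worst score on every subscale and are not affected.) No planned analysis puts the answers back. The missing-data diagnostics in Section 6.7 count and describe patients with missing BICRO-39 data, and carry-forward is reserved for mRS and GOSE.

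**Working it through.** **Inputs.** Items per subscale, from Table 8: personal care 6, mobility 6, self-organisation 6, contact with partner/children 2, contact with parents/siblings 3, socialising 6, productive employment 4, psychological well-being 6. The two conditions and the weights come from Section 5.9, and the list of analyses from Table 11.

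**Reproducing the plan's figures.**
- All items: 6 + 6 + 6 + 2 + 3 + 6 + 4 + 6 = 39, as stated.
- Items in the overall score: 39 − 2 − 3 = 34, as stated.
- Weights: 5 × 6/34 + 4/34 = 34/34 = 1, so they are coherent.
- Whole-form threshold: 50% of 39 is 19.5, so at least 20 answers are needed.

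**Applying the conditions to a form with one subscale blank and everything else answered.**

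| Blank subscale | Items answered | 50% condition | Blank-subscale condition | Result under Section 5.9 |
|---|---|---|---|---|
| Productive employment | 39 − 4 = 35 (89.7%) | met | fails | all BICRO-39 data dropped |
| Any 6-item subscale | 39 − 6 = 33 (84.6%) | met | fails | all BICRO-39 data dropped |
| Contact with partner/children | 39 − 2 = 37 (94.9%) | met | not triggered | other seven kept |
| Contact with parents/siblings | 39 − 3 = 36 (92.3%) | met | not triggered | other seven kept |
| Both contact subscales | 39 − 5 = 34 (87.2%) | met | not triggered | other six kept |

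**What the table shows.**

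1. In the first two rows the form passes the 50% count easily. The exclusion comes from the blank-subscale condition alone.
2. In those rows seven subscales are fully answered, and none is analysed. Two of the seven are the contact subscales, which have no part in the overall score.
3. The last three rows show that the SAP already accepts different patient numbers in different subscale analyses. With both contact subscales blank, a form with 34 answers keeps six subscales; with employment blank, a form with 35 answers keeps none.

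**Comparison with SF-36.** Section 5.7 has a similar pair of conditions. There, only the Physical and Mental Health scores are analysed, and each is built from all eight subscales, so a blank subscale leaves nothing analysable to lose. BICRO-39 differs because Table 11 analyses its subscales in their own right.

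**Effect of confining the exclusion.** The patient with 35 of 39 answers would keep 7 of 8 subscale scores instead of 0, and would still have no overall score.

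**The case against.** The best defence is that one rule for the whole instrument keeps the overall score and the subscales it gates on essentially the same patients. The subscales are also supplementary, on an instrument that is not a key secondary endpoint. If more than 15% of an arm lacks BICRO-39 data at Day 180, the diagnostics apply and further analyses may follow. All of this limits the consequences, but none of it requires discarding answered subscales. The gate is a rule about the overall result and works with differing patient numbers. The contact subscales can already have smaller numbers than the overall score.

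A reader might infer three stronger points, which the SAP does not support.

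- *Selection by whether a block applies to the patient*, for example productive employment. Section 5.9 places a not-applicable response among the least favourable, scored 5. Such an item is answered, so a blank block means non-response.
- *A stated loss of power.* The SAP gives no rate of blank subscales and claims no power for any BICRO-39 comparison. Its 80% in Section 3.1 is for maximum MCA flow velocity.
- *The rule is also too lenient, because one answer is enough for a subscale.* This is literally so. A form with 6, 6, 5, 1, 1 and 1 answers (20 of 39) is kept, and if employment is one of the three sparse subscales, three answers carry (6 + 6 + 4)/34 = 47% of the overall score. But full weight for sparse subscales is a deliberate choice with a stated reason. A half-of-items minimum would delete the overall score, the primary BICRO-39 analysis, for nearly complete forms: 2 of 6 answered in one subscale leaves 35 of 39 (90%), and 1 of 4 in employment leaves 36 of 39 (92%). That is a trade-off, not a correction.

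**Conclusion.** The point holds in a narrow form. Section 5.9 extends an exclusion that the overall score needs to subscale scores that do not need it. For an affected patient the loss is seven fully answered subscale scores at a visit, with 35 of 39 items answered if employment is the blank block or 33 of 39 if a 6-item block is.

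This rests on reading the exclusion as covering subscale scores as well as the overall score, which is what its wording says. How many patients would be affected is unknown and could be very few. The overall BICRO-39 analysis is untouched, and the consequences stay within supplementary, gated analyses. This is a minor improvement in the use of collected data, not an error that threatens a main conclusion.

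**What to change.** Reword Section 5.9 so that, when a contributing subscale has no answers but the 50% condition is met, only that subscale and the overall score are treated as missing at that visit. The patient's other answered subscales, including the contact subscales, stay in their own analyses as means of the recorded items. Leave the 50% condition, the weights, the scoring of deaths and the Section 6.3 gate unchanged, and report the number of patients analysed for each subscale.

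The cost is a sentence or two in the SAP and a small change to the derivation code. Patient numbers will differ somewhat more between subscales and from those behind the overall score, which the per-subscale counts make visible.
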